### Recruitment

#### Intervention group – participating practices, PNs and patients.

Participating practices were recruited between January and December 2025, while information about the PRIMA project had already been shared in the two months leading up to the project start. Recruitment was conducted by the Association of SHI Physicians of Baden-Württemberg (KVBW) through two sequential steps. First, postal letters were sent to a sample of randomly selected practices, followed by information and outreach via email to a further randomly selected sample of practices in the federal state of Baden-Württemberg, Germany. PNs employed in PRIMA were recruited by the practices themselves or via the KVBW. All PNs participating in PRIMA must have completed a three-year vocational training program as nursing professional (*Altenpfleger:in*, *Gesundheits- und Krankenpfleger:in* or *Pflegefachfrau/-mann*) and possess either an academic postgraduate qualification in nursing or at least five years of professional experience in nursing, preferably across different care settings. Alternatively, nurses who have obtained an academic qualification in nursing, such as a bachelor’s or master’s degree with a specialization in Advanced Nursing Practice could be employed. Patients eligible for participation were identified in a stepwise approach using a combined data-driven approach and clinical judgement by the GP and the respective practice team based on the inclusion and exclusion criteria. All study participants are recruited between 1 January 2026 and 30 September 2026. Eligible patients are informed about the study during routine consultations. Written informed consent is obtained by the treating GP and forwarded to KVBW prior to participation using a standardized consent form approved by the ethics committee. Where applicable, consent must be provided by a legal guardian or authorized representative.

For the PE, all study participants with the capacity to provide informed consent are invited by the PN to participate in the surveys of the PE. Recruitment of the practice teams, patients as well as their relatives and collaborators for the qualitative case studies is guided by the scientists from Institute of General Practice and Interprofessional Care, Tuebingen (IAIV) in a selective sampling approach guided by the principle of information power. Informed consent was obtained from all participants in the PE [25].

### Control group – patients and practices

The CG consists of matched patients receiving usual care in comparable general practices outside the PRIMA intervention. Patients will be identified using routine data from the KVBW and AOK Baden-Württemberg (AOK BW) databases and matched to participants in the IG at both patient and practice level. Matching criteria include demographic and clinical characteristics such as age, sex, diagnosis, and comorbidities to ensure comparability between groups. Usual care reflects standard ambulatory primary care within the German statutory healthcare system as delivered by GPs outside the PRIMA intervention. This allows a pragmatic and policy-relevant evaluation of the intervention under real-world conditions, assessing the added value of the PRIMA care model compared to standard practice without altering routine care pathways. There is no control group for the PE.

### Study timeline

The study consists of a preparation phase, an intervention phase, and an evaluation phase (Fig 1). Preparatory activities, including practice recruitment, development of study materials, training, and establishment of data management procedures, started in January 2025 and continued until December 2025. The intervention phase is scheduled from January 2026 to September 2027 and includes patient recruitment for the intervention and PE as well as the implementation of the intervention. This study was registered retrospectively on 26 April 2026 (DRKS00039104) after enrolment began, due to administrative delays during the project start-up phase. No changes to the objectives, eligibility criteria, endpoints, or statistical analysis plan were made after enrolment began. The authors confirm that all ongoing and related trials for this intervention are registered. At the time of manuscript submission, recruitment of participating patients is ongoing and expected to be completed in September 2026. Data collection will be completed in September 2027. The evaluation and analysis phase will take place between October 2027 and June 2028 and will include data analysis, reporting, and dissemination of study findings. Study results are expected in 2028.

**Fig 1 pone.0357117.g001:**
[figure not shown]
Participant timeline: Schedule of enrollment, interventions, and assessments [64]. + This time point reflects enrollment of practice teams to quantitative PE. # This time point reflects enrollment of patients to quantitative PE and practice teams to qualitative case studies. *This time point reflects enrollment of patients/relatives/collaborators to the qualitative case studies of PE.

### The PRIMA intervention

The PRIMA intervention encompasses different elements at the practice level focusing on the aspects of continuity, comprehensiveness and subsidiarity of care provided by the practices (Fig 2). Core of the intervention is the introduction of PNs with their profession-specific competencies to the existing practice team. Intervention development was guided by the CCM. The PN introduces a NCM offering services beyond regular care currently provided. Within this NCM, the PN is to deliver seven defined tasks in the care for patients with chronic conditions, namely: 1. integration of PN into regular physician-led consultations, 2. conduct of initial and follow-up assessments to support comprehensive evaluation of care in the home setting, 3. coordination of care, 4. participation in interprofessional case conferences, 5. proactive monitoring of the care trajectory, 6. provision of patient education and 7. management of patient inquiries, including acute intervention in crisis. The intervention will be delivered over the full observation period, with a minimum duration of 12 months of follow-up per patient. In order to prepare the intervention, the PNs were employed six months in advance to the start of the intervention in January 2026. Three workshops of each two full days were held before the start of the intervention to prepare the PNs for the NCM. The workshops encompassed information on the PRIMA study and its design, including information and training for the seven tasks to be delivered. Furthermore, the workshop included topics like working in multiprofessional teams, communication skills and the own understanding of the PN role within the practice team. Prior to the start of the intervention, GPs and other team members were invited to participate in two so called “network meetings” providing the participating practice teams as a whole with relevant information regarding the conduct of the study. During the intervention phase, quality circles for the PNs take place on a monthly basis to support intervention delivery. Furthermore, during the first six months of the intervention, another two-day workshop will be held. As the role of the PN with defined tasks beyond regular care is novel to the practice teams, change management support is offered. All PN patient contacts are documented by the PN in a work diary during the intervention phase. Documentation includes baseline data (e.g., age, sex, date of inclusion, presence of inclusion criteria) and reason for contact, type of contact, activities performed, provided healthcare services, time expenditure (minutes), and, where applicable, additional comments in a free-text field. All elements of the intervention are delivered by the project partner IGES in collaboration with KVBW.

**Fig 2 pone.0357117.g002:**
[figure not shown]
New care model in PRIMA.

Participating practices are offered the optional use of SmED (Strukturierte medizinische Ersteinschätzung in Deutschland, structured medical initial assessment tool), a structured software tool for medical initial assessment. SmED supports urgency assessment and facilitates allocation of patients to the most appropriate professional within the practice team.

Participants in the PRIMA study may receive any concomitant care as part of routine healthcare within the German statutory healthcare system. The intervention is delivered as part of routine primary care in participating practices and does not interfere with or restrict other aspects of patients’ healthcare utilization.

As the PRIMA intervention is an organizational care model implemented at practice level, adherence is primarily supported through structured training of participating practice teams, and PNs especially, provision of implementation support, and continuous contact with the study coordination team. No specific adherence measures are applicable for comparator patients, as the CG is based on routine data reflecting usual care without active participation requirements.

Participants will remain in the analysis population unless they withdraw consent or data availability ceases. In case of death, participants are retained in the intention-to-treat (ITT) population, and data are included up to the time of death. As the PRIMA intervention is implemented at the practice level as an organizational care model, no individual-level modification of the intervention is foreseen. Practices may discontinue participation in the intervention in case of organizational changes. However, no modifications of the intervention at individual patient level are planned.

### Outcomes

The primary outcome of PRIMA is the number of ASE after 12 months, identified using routine data from SHI physicians via standardized reimbursement codes (GOP). ASEs are defined as acute emergency contacts that are considered potentially avoidable through effective outpatient care and adequate disease management [22].

Secondary outcomes include measures of healthcare utilization, continuity and coordination of care, preventive service delivery, mortality data and economic outcomes. These are derived from routine data provided by KVBW and AOK BW.

Outcomes of the health economic evaluation include the costs of ambulatory care, defined as cumulative ambulatory care costs derived from claims data over a 12-month follow-up period, as well as intervention costs incurred during this period (including costs related to the PN intervention). In addition, cost-effectiveness will be assessed by relating total costs to the number of ASE.

Outcomes are assessed either over 12 months or across the full intervention period and obtained from routinely collected claims data made available by the KVBW and AOK BW following completion of the observation period. They are listed in Table 2 together with their respective data sources and assessment timeframes.

**Table 2 pone.0357117.t002:** Overview of study outcomes, data sources, and measurement periods.

Primary outcome				
Level	Outcome	Definition	Data source	Timeframe
Micro	Ambulatory care–sensitive emergencies (ASEs)	Number of ASEs identified via billing codes (GOP 01210 and 01212); indicator of potentially avoidable emergency care	KVBW routine data	12 months

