**Secondary outcomes – KVBW data**				
Micro	ASE per person-year	ASE rate adjusted for patient-specific observation time	KVBW	Intervention period
Micro	Patients with ≥1 ASE	Proportion of patients with at least one ASE	KVBW	12 months
Micro	Ambulatory emergencies	All emergency contacts independent of diagnosis	KVBW	12 months
Micro	Ambulatory emergencies per person-year	Rate-adjusted emergency contacts	KVBW	Intervention period
Micro	GP utilization	Number of GP contacts / quarters with GP visits	KVBW	Intervention period
Micro	Specialist utilization	Number of specialist contacts / quarters	KVBW	Intervention period
Meso	Treatment intensity	EBM points per patient and per practice	KVBW	Intervention period
Meso	Continuity of care	Continuity-of-Care Index (e.g., Bice–Boxerman)	KVBW	Intervention period
Meso	Care coordination	Number of providers; referral-based specialist visits	KVBW	Intervention period
Micro	Preventive care	Vaccination rates (influenza, pneumococcal, COVID-19)	KVBW	Intervention period
Macro	Outpatient costs	Cumulative outpatient costs incl. intervention costs	KVBW	12 months
Macro	Outpatient cost-effectiveness	Cost per outcome achieved	KVBW	12 months

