**Secondary outcomes – AOK Baden-Württemberg data**				
Macro	ASE + ambulatory-sensitive hospitalizations	Combined outpatient and inpatient avoidable emergency events	AOK BW	12 months
Macro	ASE + hospitalizations per person-year	Rate-adjusted combined events	AOK BW	Intervention period
Macro	Total emergencies	Diagnosis-independent emergency contacts	AOK BW	12 months
Macro	Total emergencies per person-year	Rate-adjusted total emergencies	AOK BW	Intervention period
Macro	Ambulatory-sensitive hospitalizations (ASH)	Potentially avoidable hospital admissions	AOK BW	12 months
Macro	ASH per person-year	Rate of ASH	AOK BW	Intervention period
Macro	Overall survival	Mortality data	AOK BW	Intervention period
Macro	Guideline adherence	Medication prescribing patterns	AOK BW	Intervention period
Macro	Total healthcare costs	All-cause expenditure	AOK BW	12 months
Macro	Overall cost-effectiveness	System-level cost-effectiveness	AOK BW	12 months

The PE encompasses outcomes on the micro- and the meso-level, namely participating patients and their relatives as well as the practice teams. The (PE) evaluation comprises both quantitative and qualitative measures. Table 3 gives an overview of the outcomes. All validated questionnaires have been used in primary care settings, targeting either interprofessional teams or patients with chronic conditions, aligning with the objectives of this study. Self-developed questionnaires were piloted with representatives of the target population using the think-aloud method to assess comprehensibility, relevance, and usability. Findings from the pilot testing informed revisions of the questionnaires before their use in the study [26].

**Table 3 pone.0357117.t003:** Outcomes of process evaluation on Meso and Micro Level.

Meso Level (Practice Teams)						
Outcomes	Instrument	B	T0	T1	T2	P
Job satisfaction	Warr-Cook-Wall (WCW) [40–42]	x		–	X	PT
Interprofessional Collaboration	Assessment of Interprofessional Team Collaboration Scale (AITCS-II) [7,43,44]	x		–	X	PT
Interprofessional Socialization	Interprofessional Socialization and Valuing Scale (ISVS 9a + 9b) [45,46]	x		–	x	PT
Implementation fidelity	Self-developed Questionnaire	–	–	–	x	PT
	PN documentation (activity logs)				x	PN
	Qualitative Case Study (interviews, focus groups, qualitative activity logs)			x	x	PT/C
PN training	Self-developed questionnaire based on ICAP model and Kirkpatrick levels [47–49]		x		x	PN

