#### Effectiveness evaluation.

The primary endpoint (number of ASE after 12 months) will be analyzed according to the ITT principle. The ITT population of the IG comprises all patients enrolled in the NCM by the end of the nine-month recruitment period, receiving at least 12 months of care. The smallest unit of analysis is the individual patient, as outcomes are assessed at patient level. In a baseline analysis, sociodemographic and clinical characteristics of the IG will be compared with those of the matched CG to assess the effectiveness of the matching procedure and identify potential determinants of the study endpoints [34,35]. The significance of the differences will be tested using linear mixed models for continuous variables with normal distribution, logistic models for binary variables, and the chi-square test and Fisher’s test for categorical variables. Subsequently, the rate of ASE in the IG and CG will be analyzed using multi-level regression models with patients nested within practices to account for the hierarchical structure of the data [36]. As a sensitivity analysis, models with cluster-robust standard errors at the practice level will be estimated. Relevant covariates identified in the initial analyses will be included in adjusted regression models [37].

Continuous secondary endpoints, including healthcare costs, will be analyzed using adjusted mixed linear models. Mortality will be assessed using survival analyses, while binary outcomes will be analyzed using generalized linear mixed models. Covariates will be selected analogously to the primary analysis. Extensive sensitivity analyses are planned to assess the robustness of the evaluation parameters. The choice between matched datasets derived from KVBW or AOK-BW routine data will depend on the respective endpoint as specified in Table 2. Statistical significance will be defined as a two-sided p-value <0.05. Where relevant, 95% confidence intervals are provided.

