### Missing data

Missing data are expected to be minimal, as outcome data are derived from routinely collected administrative healthcare databases (SHI and KV data). Nevertheless, incomplete follow-up may occur due to changes in insurance status, migration outside the data capture area, or death. Such missingness will primarily result in right-censoring of observation periods. Analyses will account for this using appropriate model-based approaches inherent to survival and mixed-effects regression models, which allow inclusion of all available observations under a missing-at-random assumption conditional on observed covariates. No imputation will be performed for fully missing outcome periods; however, sensitivity analyses will be conducted to assess the robustness of results to potential informative censoring. For the quantitative part of the PE, multiple imputation approaches will be applied if needed.

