Potential unintended effects should also be considered. The introduction of new professional roles and structured care processes may initially increase coordination demands within practice teams. On the patient level, uncertainty regarding the respective roles of nursing professionals and physicians may occur during early implementation phases. Furthermore, improved access and proactive care management could temporarily increase consultation rates and affect economic evaluation.

Voluntary participation may also introduce selection bias, as practices with a stronger interest in innovation and team-based care may be more likely to participate, which should be considered when interpreting the generalizability of the findings. In addition, the 12-month follow-up period may be insufficient to detect longer-term effects, particularly regarding healthcare utilization and costs. Potential drop-outs at both practice and patient level, including staff turnover and loss to follow-up, may affect study implementation and outcome assessment. These risks were considered in the study planning and sample size calculation. The use of separate routine data sources from AOK BW and KVBW, which are not linked at the individual level, limits the possibility of fully integrated analyses. Moreover, the validity of the matched CG depends on the availability of routine data variables and the applied matching procedure, which may not fully account for residual differences between groups. However, matching considerably improves the comparability of both groups by reducing observable baseline differences.

Despite these limitations, the study has considerable transfer potential. Owing to the relatively uniform structure of the German statutory healthcare system, the findings are expected to be highly transferable within Germany. The results may also be relevant internationally, as many healthcare systems face similar challenges related to multimorbidity, workforce shortages, and the growing need to strengthen primary care. However, transferability to other countries will depend on the organization of primary care, financing structures, and the regulatory scope of practice for nursing professionals. The accompanying PE will therefore be essential for interpreting implementation and effectiveness across different contexts. In this regard, PRIMA may serve as a blueprint for future initiatives aimed at strengthening multiprofessional and team-based primary care models.

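### The mixed model said to handle right-censoring cannot do so for a single 12-month cost total per patient, so cost differences and both ICERs can be biased by loss of patients who are still alive

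*Protocol article*

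**What the plan says.** Under Outcomes, ambulatory cost is "cumulative ambulatory care costs derived from claims data over a 12-month follow-up period", with intervention costs in the same period added. In Table 2 the KVBW cost row reads "Cumulative outpatient costs incl. intervention costs" and the AOK BW row reads "All-cause expenditure". Both carry a 12-month timeframe, as do the two cost-effectiveness rows.

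The model is named under Effectiveness evaluation: "Continuous secondary endpoints, including healthcare costs, will be analyzed using adjusted mixed linear models". No exposure term, weighting or other device for incomplete cost histories is named with it.

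The Missing data section expects that "incomplete follow-up may occur due to changes in insurance status, migration outside the data capture area, or death" and describes the result as right-censored observation periods. The remedy follows: "Analyses will account for this using appropriate model-based approaches inherent to survival and mixed-effects regression models". It adds that these models use whatever observations exist under a missing-at-random assumption, that wholly missing outcome periods are not imputed, and that sensitivity analyses will examine informative censoring.

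Two other places bear on who is analysed. The section on the PRIMA intervention keeps participants until consent is withdrawn or their data stop, and uses the data of those who die up to death. Effectiveness evaluation describes the ITT set of the intervention group as enrolled patients with at least 12 months of care.

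The Health economic evaluation relates ambulatory costs (KVBW) and total costs (AOK BW) to the number of ASE as ICERs.

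**The concern.** A mixed-effects model copes with dropout under missing at random when each patient contributes several measurements, because the observed ones inform the model about the rest. Here each patient contributes one number. If observation stops at month 4, that number is four months of cost, and nothing in the model marks it as different from a full year. The random effect for practice absorbs between-practice variation and does not restore the missing eight months. The stated remedy therefore does not work for the cost endpoints as they are defined.

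The cost difference is the numerator of both ICERs. There is also a reason why loss could differ between arms. Intervention patients give consent and can withdraw it, whereas controls are drawn from routine data and have nothing to withdraw. A difference in loss of data could then appear as a saving or an extra cost that the care model did not cause.

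**Working it through.** **No cost figure to reproduce.** The article states no mean cost, standard deviation, ICER or loss rate by arm. What follows shows how the mechanism behaves under stated assumptions.

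**Inputs from the article (Sample size calculation).** Baseline rate 0.20 ASE per patient-year and a 15% reduction, so 0.20 × 0.85 = 0.17 under the intervention and 0.03 ASE averted. The 10% patient-level dropout is the only loss figure given. It is an allowance for sample size, not a forecast of claims truncation.

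**Assumptions (not in the article).** Annual cost 4,000 in controls and 4,300 in the intervention group (true increment 300). A share d of an arm is lost alive, evenly over the year and unrelated to cost. Lost patients are kept with what was observed.

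**Formulas.** Expected observed total in an arm = C × (1 − d/2).
- Numerator = 4,300 × (1 − d1/2) − 4,000 × (1 − d0/2)
- ASE averted = 0.20 × (1 − d0/2) − 0.17 × (1 − d1/2)
- ICER = numerator ÷ ASE averted

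Here d0 is loss in controls and d1 is loss in the intervention group. With practices of equal size, the arm effect of a linear mixed model on one total per patient is the difference in arm means, so these formulas describe what that model would estimate.

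**No loss.** 300 ÷ 0.03 = 10,000.

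**5% control, 10% intervention.** Numerator 4,300 × 0.95 − 4,000 × 0.975 = 4,085 − 3,900 = 185. ASE averted 0.195 − 0.1615 = 0.0335. ICER 185 ÷ 0.0335 = 5,522.

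**Other patterns**

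| Loss, control / intervention | Numerator | Change | ASE averted | ICER |
|---|---|---|---|---|
| 10% / 10% | 285 | −5% | 0.0285 | 10,000 |
| 5% / 10% | 185 | −38% | 0.0335 | 5,522 |
| 10% / 5% | 392.5 | +31% | 0.02425 | 16,186 |
| 2% / 10% | 125 | −58% | 0.0365 | 3,425 |
| 10% / 2% | 457 | +52% | 0.0217 | 21,060 |

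**Sensitivity to the assumed increment.** With a true increment of 800, the same unequal patterns change the numerator by −25% to +19%. The larger the true increment relative to annual cost, the smaller the relative error.

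**Simulation check.** With 20 practices of 112 patients per arm, 400 runs and loss unrelated to cost, truncated totals missed the full-follow-up difference by about −14 (10% / 10%), −117 (5% / 10%), −171 (2% / 10%) and +158 (10% / 2%). The formulas give −15, −115, −175 and +157.

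**Equal loss cancels only if ASE is truncated too.** Effectiveness evaluation speaks of analysing the ASE rate. If the denominator were a rate at the full 0.03 while costs were truncated totals, equal 10% loss would give 285 ÷ 0.03 = 9,500, which is 5% low.

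**If lost patients are dropped instead.** The truncation formula no longer applies. When loss is unrelated to cost, the complete cases give the right mean with less precision. When loss is related to cost, complete cases are a selected group and the difference can be biased in either direction.

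**The case against.** A reader might infer that every patient lost early will count as a cheap patient and that both ICERs are therefore biased. The article does not support that.

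- It never says that a truncated total enters as a full year. The rule that participants leave when their data stop, and the ITT description requiring 12 months of care, can be read as removing patients lost alive. The Missing data section, which uses whatever observations exist, points the other way. The text does not settle it.
- Nobody is censored administratively before 12 months: recruitment ends on 30 September 2026 and the data run to 30 September 2027.
- Costs up to death are complete 12-month costs, because nothing is spent afterwards. Listing death with fund change and migration does not make a decedent's total censored.
- A fund change should end AOK BW data but need not end KVBW outpatient claims. This is an inference from the data sources, but it means the two ICERs are not equally exposed.
- The article expects little missing data, and stopping use of the care model need not end a patient's claims.
- Sensitivity analyses for informative censoring are planned, and the exact cost estimator may stand in an analysis plan that is not shown.

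All of this limits the size of the problem and leaves its direction open. It does not rescue the stated remedy. The planned sensitivity analyses address informative censoring, whereas truncated totals go wrong under non-informative loss as soon as it is unequal. An unseen plan may name a better estimator, but the article already names a model and says that models of this kind deal with censoring.

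Two further inferences also go too far. Because Table 2 offers "ASE rate adjusted for patient-specific observation time" for events, a reader might ask for cost per person-year as well; annualising the costs of those who die would itself distort the mean. And because the limitations say that "the 12-month follow-up period may be insufficient to detect longer-term effects, particularly regarding healthcare utilization and costs", a reader might call the 12-month cost window an error. It is a disclosed choice that matches the primary endpoint.

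**Conclusion.** The point holds in a limited form. For costs defined as one 12-month total per patient, the statement that mixed-effects models account for right-censoring is wrong, and the article leaves open whether patients lost alive are kept with truncated totals or dropped. Bias in the cost difference and the ICERs is possible, not established. It needs loss that differs between arms (if totals are truncated) or loss that is related to cost (under either handling). The AOK BW total-cost ICER is probably more exposed than the KVBW one.

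Under the assumed annual cost of 4,000 and true increment of 300, a five-point imbalance moves the ICER from 10,000 to about 5,500 or about 16,200, depending on which arm loses more. Equal loss leaves it at 10,000 if ASE counts are truncated in the same way. The cost level, the increment and the imbalance are assumptions, so these figures show sensitivity and do not forecast the trial's result.

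**What to change.** 1. Reconcile the three statements on who is analysed (the section on the PRIMA intervention, Effectiveness evaluation, Missing data), and say explicitly what happens to the costs of a patient whose data stop while alive.
2. Define 12-month costs as complete at death, with zero cost afterwards, and as censored at fund change, migration or withdrawal.
3. Replace the naive total with a censoring-adjusted estimator: costs partitioned by quarter, which suits the quarterly extraction described under Data, or inverse-probability-of-censoring weighting of the 12-month total.
4. Apply the same censoring rule to the ASE denominator of both ICERs, so that numerator and denominator refer to the same follow-up.
5. Limit the claim about mixed-effects models in the Missing data section to outcomes for which it is true.

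The cost is revised wording, some programming and slightly wider intervals than naive totals would give. It uses data already requested and needs no further patients, and analysis does not begin until October 2027.
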